### Data management

Our app allows for various types of input, including all above-mentioned validated migraine questionnaires, a daily headache diary, and a digital nutrition diary. This data is stored in a local, encrypted database on the user’s device and is securely synchronized to Perfood servers, where it is stored encrypted, backed up regularly, and accessible only by specifically trained people following Perfood’s SOPs. All servers reside in Germany fulfilling high standards regarding security and stability required by law for DTx in Germany.

CGM data are collected on the reading devices from the CGM manufacturer and then are transferred by the users to enter our servers. CRF data are independently digitalized twice in order to avoid errors.

All data is checked for consistency and data value ranges. Questionnaires can only be submitted if all mandatory fields are filled out. All data processing is tested using unit and system tests. The final database is archived in a way to ensure a minimum of 10 years.

### Endpoints

The primary efficacy endpoint of this study is the change in the number of days with migraine symptoms in the past 4 weeks at 12 weeks after intervention in IV or after randomization in CO compared with baseline. For this, days with migraine headache are counted from the electronic headache diary of the past 4 weeks at baseline and at follow-up 12.

Secondary efficacy endpoints are:Change in the number of days with migraine symptoms at follow-up 12 compared with baseline after exclusion of non-adhering patients in IVResponse as indicated by a relative reduction of the number of migraine days assessed by the eDiary in 4 weeks at follow-up 12 by 30% compared with baselineChange in the limitations in daily life (assessed by HIT-6) at follow-up 12 compared with baselineChange in the headache-caused disability (migraine disability, assessed by MIDAS) at follow-up 12 compared with baselineChange in the quality of life (assessed by EQ-5D-5L) at follow-up 12 compared with baselineChange in the days with acute migraine-specific medication (assessed by eDiary) at follow-up 12 compared with baseline

Exploratory endpoints will include the change in the number of days with migraine symptoms, the response, the change in headache-caused disability, and in acute migraine-specific medication defined above at earlier time points, i.e., at follow-ups 4 and 8.

Furthermore, at all time points, the following endpoints compared with baseline will be assessed:Response as indicated by a relative reduction of the number of migraine days in 4 weeks by 50% compared with baseline (eDiary),Change in number of days with non-migraine headaches of moderate or severe intensity in the past 4 weeks (eDiary),Change in number of migraine attacks in the past 4 weeks (eDiary),Change in maximal headache pain intensity in the past 4 weeks (eDiary),Change in cumulative length in hours of migraine attacks in the past 4 weeks (eDiary),Change in cumulative length in hours of non-migraine headache in the past 4 weeks (eDiary),Change in self-assessment on health state (EQ-VAS),Change in missed days at work, school, or equivalents in the past 4 weeks (MIDAS),Change in productivity at work, school, or equivalents in the past 4 weeks (MIDAS),Adherence to existing medication (MARS),Assessment on impression of change in symptoms (Patient Global Impression of Change, only follow-up 12), andChange in number of days without headaches in 4 weeks (eDiary)

Adherence endpoints will be assessed to evaluate how strictly the patients adhered to the recommendations at the end of every week of intervention, totaling 12 time points. At each of these time points, the number of days a specific meal (breakfast, lunch, dinner, snack, beverage) was consumed is assessed as well as the number of days the recommendations for the specific meal were largely followed. From this, the total number of meals per week and the percentage of meals with followed recommendations are computed for every patient. From this, a patient will be defined to be non-adherent if the percentage of meals with followed recommendations is < 50%.

As safety endpoints, all adverse events (AEs) and serious adverse events (SAEs) as well as adverse device effects (ADEs) will be monitored.

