### Study design

The study is a randomized, open-label, intervention study controlled against the standard of care. The study is planned as a monocentric study, so that every study participant has the same examination conditions and no standardization across several study centers is necessary. However, all visits are organized digitally using telemedicine techniques qualifying the study as “decentralized.”

The study design follows the recommendations of the International Headache Society for conducting trials of medications for prophylaxis in patients with episodic migraine and the recommendations for the use of health technologies in the treatment of migraine [21, 22].

After qualification in a 4-week pre-study (baseline phase) for the main study, the study participants will be randomized 1:1 to IV and CO. The intervention is the application of the DTx sinCephalea, which determines the personalized nutritional recommendation using data from a 10-day long continuous glucose monitoring (CGM) test phase followed by a 12-week nutritional intervention.

The control group represents the non-application of the DTx according to the standard of care. Like in the intervention group, the study endpoints are also collected electronically via the smartphone. In the sense of a waiting control group, the control group is offered the use of the DTx after completion of the study outside of the protocol.

The current standard of care in Germany is that patients with migraine do not have access to a prescription non-drug treatment option. The established treatment of migraine shall be continued unchanged (standard treatment, “standard of care”).

The study design is also displayed in Figure 1 using the SPIRIT reporting guidelines [23].

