### Main study

After randomization, the main study comparing IV with CO begins. The use of the DTx represents the treatment in the IV phase after randomization. The DTx determines the personalized nutritional recommendation using data from a 10-day long CGM test phase followed by a 12-week nutritional intervention. The structure of the intervention phase is the same for all patients in IV, but the implemented nutritional recommendations are personalized.

A test kit and the use of one of the validated tissue glucose sensors (Dexcom G6 sensor and Abbott FreeStyle Libre sensors 1 and 2) are required for the IV. Immediately after randomization, the study site sends the test kits to the patient. After receiving the test kit, the individual test phase begins. For this purpose, the tissue glucose sensor is first applied according to the manufacturer’s instructions and remains there for at least 10 days. At the same time, food intake and other events such as sleep, everyday movement, and physical activity are recorded via the app. The state of health, stress, and migraine-specific symptoms are also logged via the app. The participants continue their usual eating habits and test the meals they like and eat frequently.

All data will be computed by Perfood GmbH in accordance with the sponsor’s internal SOPs, and the personalized nutrition recommendations are sent to the individual patients via their app. Immediately after receipt, consultations with nutrition experts are conducted voluntarily to ensure that the patient correctly understands all recommendations and are able to adjust his diet accordingly. Recommendations are also well explained in the app, ensuring understanding of the recommendations even if nutritional consulting is not realized. The intervention phase, in which the personalized nutritional recommendations are implemented, lasts 12 weeks until the endpoint is recorded. It thus represents the actual migraine prophylaxis by adhering to the personalized low-glycemic diet.

The CO is the non-application of the DTx while continuing the standard treatment. The study participants are provided with an app through which only the study-relevant questionnaires can be used. This ensures that there is no difference between the groups regarding the mode of assessment of the patient-reported outcomes. After the follow-up after 12 weeks and the individual end of the study, the DTx can be used.

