## Abbreviations

ADE: Adverse device effect
AE: Adverse event
BfArM: Federal Institute for Drugs and Medical Devices for German “Bundesinstitut für Arzneimittel und Medizinprodukte”
CGM: Continuous glucose monitor/monitoring (validated are the Dexcom G6 sensor and Abbott FreeStyle Libre sensors 1 and 2)
CIP: Clinical investigation plan
CO: Control group
CRFs: Clinical reporting forms
DiGA: Digital health application for German digitale Gesundheitsanwendung
DTx: Digital Therapeutics
DVG: Digital healthcare act for German Digitale-Versorgung-Gesetz
eDiary: Electronic diary
FA: Full analysis
FU12: Follow-up week 12 after intervention in IV or after randomization in CO
GDPR: EU General Data Protection Regulations
HIT-6: Headache Impact Test 6-item
ITT: Intention to treat
IV: Intervention group
GDPR: General Data Protection Regulations
MAR: Missing at random
MARS: Medication Adherence Report Scale
MCAR: Missing completely at random
MIDAS: Migraine Disability Assessment
MNAR: Missing not at random
PGIC: Patient Global Impression of Change
PI: Principal Investigator
PID: Patient identification
PP: Per protocol
SA: Safety analysis
SAE: Serious adverse event
SAP: Statistical analysis plan
SOPs: Standard operating procedures
ZKS: Zentrum für Klinische Studien Lübeck (Center of Clinical Studies)

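### The 12-week endpoint is timed from the start of the diet in IV but from randomization in CO, so the primary comparison uses diary windows at least 10 days apart and assumes, without saying so, no late time trend

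*Protocol article*

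**What the plan says.** The Endpoints section defines the primary endpoint as the change in migraine days "in the past 4 weeks at 12 weeks after intervention in IV or after randomization in CO compared with baseline". The abbreviation list repeats the two origins: "FU12: Follow-up week 12 after intervention in IV or after randomization in CO". The study objectives and the missing-data section use the same split.

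The Main study section gives the order of events in IV:

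- "Immediately after randomization, the study site sends the test kits to the patient".
- "After receiving the test kit, the individual test phase begins".
- In that phase "the tissue glucose sensor is first applied according to the manufacturer’s instructions and remains there for at least 10 days", while the patient keeps to usual eating habits.
- The data are then computed and the recommendations sent through the app.
- Only then does the diet start: "The intervention phase, in which the personalized nutritional recommendations are implemented, lasts 12 weeks until the endpoint is recorded".

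The Study design section describes the same order, "using data from a 10-day long continuous glucose monitoring (CGM) test phase followed by a 12-week nutritional intervention". The adherence endpoints fit this reading, with 12 weekly time points. CO has a questionnaire-only app and no matching lead-in. After its 12-week follow-up, a CO participant may use the DTx.

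**The concern.** Randomization makes the arms comparable at the moment of allocation. That comparability carries over to a later outcome if both arms are measured at the same time since allocation. Here IV is measured later, from an origin that differs between patients and depends on events after randomization (delivery, sensor wear, processing). Anything that moves migraine days with time, such as regression to the mean, the effect of keeping a diary or season, can then enter the treatment contrast. The primary model contains only treatment, sex and baseline, and none of the listed sensitivity analyses aligns the windows.

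The Discussion argues that the effects of taking part and of logging symptoms may act in both groups and so need not bias the comparison. That argument needs equal follow-up, and IV logs for at least 10 days longer before its endpoint.

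A second gap follows from the same definition. IV patients who never start the intervention are removed only from the per-protocol set. They stay in the full analysis and intention-to-treat sets, but a window counted from the start of the diet gives them no date.

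**Working it through.** **Plan's own figure.** Inputs from the Sample size section: reductions of 2.13 days (IV) and 1.14 days (CO), 20% drop-out counted as zero change, SD 3.19, two-sided alpha 0.05, power 0.8.

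- Planned difference before drop-out: 2.13 − 1.14 = 0.99 days.
- After drop-out: 0.8 × 2.13 − 0.8 × 1.14 = 1.704 − 0.912 = 0.792 days.
- The t-test solution is 255.63 per group, rounded up to 256. The stated 256 reproduces; the timing issue does not touch it.

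**Windows.** Let L be the days from randomization to the start of the diet. The CO endpoint is on day 84, with window 57–84. The IV endpoint is on day 84 + L, with window (57 + L) to (84 + L). Overlap = max(0, 28 − L). The protocol supports only L ≥ 10; the larger values are assumptions, because shipping and processing times are not given.

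| L (days) | IV window | Shared days of 28 |
|---|---|---|
| 10 (minimum) | 67–94 | 18 (64%) |
| 14 (assumed) | 71–98 | 14 (50%) |
| 21 (assumed) | 78–105 | 7 (25%) |
| 28 (assumed) | 85–112 | 0 |

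**What the offset could be worth.** The Sample size section gives a mean CO change of 1.14 days and no time course, so the shape has to be assumed.

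*Linear and continuing.* Offset effect = (1.14 / 84) × L.

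- L = 10: 0.14 days; 0.136 / 0.99 = 14%.
- L = 14: 0.19 days, 19%.
- L = 21: 0.29 days, 29%.
- L = 28: 0.38 days, 38%.

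At half that slope, L = 10 gives 0.07 days (7%) and L = 21 gives 0.14 days (14%).

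*Levelling off.* Suppose the change builds up with a 2-week half-life and reaches 1.14 days at week 12. The asymptote is 1.14 / (1 − 2⁻⁶) = 1.158, and the part still to come after week 12 is 1.158 × 2⁻⁶ = 0.018 days. Ten days (1.43 weeks) later, 0.018 × (1 − 2^(−1.43/2)) = 0.007 days have been added; after 28 days, 0.018 × (1 − 2⁻²) = 0.014 days. Both are about 1% of 0.99.

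*Flat from week 8.* Zero, because the CO window opens on day 57.

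**The case against.** The strongest reply is that the offset is deliberate and probably small. The stated objective is the effect after 12 weeks of intervention, and timing IV from the diet secures that exposure. Regression to the mean after selection on at least 3 baseline migraine days should show mostly in the first weeks, so little may be left by week 12. Both points stand. They limit the likely size, but the comparison still rests on an assumption about late trend that the plan does not make explicit.

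A reader might infer a built-in bias in favour of the DTx worth 19–38% of the planned effect. The documents do not support that. It needs both an assumed lead-in of 2–4 weeks and a decline that stays linear beyond week 12. The direction is open too: a seasonal shift could act either way, and longer follow-up in IV may produce more missing diaries, which the primary analysis imputes from CO.

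A reader might also infer that never-starters are treated as missing. The protocol does not say so. It sets the endpoint to missing only when fewer than 22 of 28 diary days are filled, and further rules may stand in the investigation plan or SAP. What stands is that the definition as written gives these patients no origin.

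It can be said that the Study design section counts the glucose test phase as part of the intervention. Even if the IV clock started there, kit delivery would still separate it from randomization.

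Finally, results at follow-ups 4 and 8 will show something of the CO time course. They are exploratory, are not tied to this question, and give no CO data after day 84, where the IV window extends.

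**Conclusion.** The point holds as a should-fix. The two origins and the order of events in IV are fixed by the protocol, so the minimum offset of 10 days and the maximum overlap of 18 of 28 days need no assumption beyond reading the IV clock as starting with the diet, which the Main study section supports. The effect on the treatment contrast cannot be determined from the document in size or direction. The illustrations run from about zero, if the CO course is flat from week 8, to 0.14 days (14% of 0.99) at the minimum offset under a linear continuing decline, and to 0.19–0.38 days only if a 2–4 week lead-in is assumed as well. A confirmatory comparison should not depend on an unstated no-trend assumption when daily diaries allow it to be checked. The same offset applies to all secondary endpoints at 12 weeks.

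**What to change.** 1. **Participants still to be followed.** Extend the questionnaire-only period in CO by a fixed lead-in equal to the planned IV lead-in, so that the 12-week assessment falls at about the same time since randomization while IV keeps 12 weeks of diet. The cost is a few more weeks of diary and waiting in CO. Some mismatch remains, because actual delivery and processing times vary. This cannot be done for CO participants who have already moved on to the DTx; the article describes the trial as still recruiting, so the sooner this is decided, the more participants it covers.
2. **All participants.** Prespecify, as a key supportive analysis of the primary endpoint, the change scored on days 57–84 since randomization in both arms. It uses diary data that are collected anyway. It is not a free replacement for the primary analysis: by day 84 an IV patient has had at most 84 − 10 = 74 days of diet (10.6 weeks), or 56 days (8 weeks) if the lead-in were 28 days, so the effect will probably be slightly smaller. Agreement between the two analyses would be reassuring; a gap would need to be read with the shorter exposure in mind.
3. **IV never-starters.** State a randomization-based 12-week window for them, so that diary entries they did make are used in the full analysis and intention-to-treat sets. The cost is one sentence.

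The sample-size inputs need not change if CO follow-up is extended.

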### Quality control and quality assurance

The study-independent quality control and assurance is ensured by monitoring of the Center of Clinical Studies (ZKS, Zentrum für Klinische Studien) Lübeck. The risk-based monitoring is performed according to ISO 14155:2020 as well as own SOPs.

### Statistical analysis

For all analyses, all patients will be considered who were successfully randomized and gave their informed consent.

The primary endpoint and other efficacy endpoints will be evaluated in the full analysis (FA) set in which patients, in whom it becomes apparent after randomization that they have either (1) headaches other than migraine or tension-type, if the latter led to more than 50% of the headache days per month; or (2) 14 or more days with migraine headaches per month, are excluded. As a sensitivity analysis, all efficacy endpoints will be additionally evaluated in the intention to treat (ITT) and per protocol (PP) populations. Here, PP additionally excludes patients in whom the intervention was not started, who did not adhere to the recommendations as defined above, changed prophylactic treatment with change of the dose, a switch to another medication, or addition of another medication, or entered no data after the first 4 weeks of IV/CO. Safety endpoints will be evaluated in the safety analysis (SA) set that includes all randomized patients, but patients in IV in whom the intervention was not started or who did not adhere to the recommendations are analyzed as CO participants.

All variables at all time points and all defined primary, secondary and exploratory endpoints (i.e., changes from baseline to follow-up visits) will be described according to their type (measurement, normal, log-normal, ordinal, proportion) using standard metrics in all analysis sets. The disposition of patients will be described by a CONSORT flow chart.

For the primary objective regarding the primary efficacy endpoint, the primary hypothesis will be tested using a linear model in the FA analysis set. With *y*_*i*_ denoting the endpoint “change in the number of days with migraine symptoms at 12 weeks” in patient *i*, the linear model is defined as follows:$${y}_i={\beta}_0+{\beta}_1{x}_i^{\textrm{Treat}}+{\beta}_2{x}_i^{\textrm{Sex}}+{\beta}_3{x}_i^{\textrm{Baseline}}+{\varepsilon}_i,$$where

$${x}_i^{\textrm{Treat}}=\left\{\begin{array}{cc}\ 0,&\ \textrm{if}\ \textrm{CO},\\ {}\ 1,& \textrm{if}\ \textrm{IV}\end{array}\right.$$, $${x}_i^{\textrm{Sex}}=\left\{\begin{array}{cc}\ 0,&\ \textrm{if}\ \textrm{male},\\ {}\ 1,& \textrm{if}\ \textrm{female}\end{array}\right.$$, and $${x}_i^{\textrm{Baseline}}$$ is given by the number of days with migraine symptoms at baseline.

We test the hypotheses H0: *β*_1_ = 0 vs. H1: *β*_1_ ≠ 0with a linear model assuming variance homogeneity using a two-sided Wald test at significance level *α* = 0.05. The corresponding 95% Wald confidence interval will be estimated.

A sequential testing procedure will be used to maintain a family-wise type I error of 0.05 for primary and secondary endpoints. If the primary endpoint is statistically significant at *α* = 0.05, the secondary efficacy endpoints will be tested. Hence, positive results on secondary endpoints can be interpreted inferentially only if a treatment effect is shown on the primary endpoint (gate-keeping).

As a further gate-keeping test, the first secondary endpoint (change in the number of days with migraine symptoms at follow-up 12 compared with baseline after exclusion of non-adhering patients in IV) is tested first at *α* = 0.05. If this is significant, the other five secondary endpoints will be tested with significance levels adjusted according to Bonferroni-Holm [42]. If any null hypothesis is rejected, a difference between IV and CO in the respective endpoint is shown. If the null hypothesis is not rejected, it will not have been shown that there is a difference.

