### Baseline assessment (pre-study)

After inclusion in the pre-study, there is a 4-week baseline phase for the prospective recording of the disease severity and for securing the inclusion/exclusion criteria as well as compliance (measured by the frequency of completion of the questionnaires required for the study and the headache diary for measuring the relevant endpoints). This ensures suitability according to the inclusion and exclusion criteria as well as sufficient cooperation for the valid collection of the endpoint-relevant patient-reported outcomes. This approach follows the recommendations of the International Headache Society for conducting studies on prophylactic treatments for episodic migraine [21, 22].

For participation at randomization and inclusion in the main study, the following inclusion criteria apply additionally:Complete answering of all questionnaires of the baseline phase (all questions)Use of headache diary on at least 80% of days in baseline phase (at least 22 of 28 days, daily questioning whether symptoms were present)At least 3 reported migraine days according to inclusion criteria during the baseline phase (4 weeks).

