### Randomization

Stratified permuted block randomization is used with stratification by gender and number of migraine days reported over the past 4 weeks (<8 days vs. ≥8 days). The block lengths are fixed and documented at the Institute of Medical Biometry and Statistics, University of Lübeck (IMBS), but are not available to those who enroll participants or assign interventions. MersenneTwister is used as a random number generator based on a real random seed from www.random.org. For the generation of the allocation sequence, RITA (version 1.50) is used.

A 1:1 randomization will be carried out. The randomization takes place centrally at the IMBS. At the beginning of the study, all future participants are randomized at once (list randomization). During the study, after enrolment of a single participant, a randomization form is filled in by the study center and sent (via fax or email) to the IMBS. This form includes the study ID, information on the strata, inclusion and exclusion criteria, name of the investigator, date and signature. At the IMBS, the validity of the enrolment is checked. If correct, the participant is registered in a data base, and the next allocation in the respective strata combination is selected. The allocation is noted on the randomization form, which is then signed and sent back to the study center.

Given the complex nature of the intervention, a blinding of the patients is not possible. The primary and secondary endpoints are based on patients’ assessment and therefore are not blinded.

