### Sample size

The sample size was calculated with the aim to show a difference in the change in the number of days with migraine symptoms in the past 4 weeks at follow-up 12 compared with baseline.

To estimate the possible effect in the control group, eight studies were identified in which migraine patients in a control group received standard care or were placed in a waiting group [24–31]. These control patients were all aware of being in a control group, which is comparable to the planned study situation. Mean changes in migraine days with corresponding standard deviations and sample sizes were extracted from these publications and meta-analyzed using a random effects model. This yielded a pooled estimate of the mean change of 1.14 days.

The sample size was then calculated based on the following assumptions:Patients in the control group will experience a reduction similar to the reduction observed in the control groups in the literature, which was a reduction by 1.14 days on average.Patients in the intervention group will experience a reduction of at least 50% on average, which is recommended to be the minimally relevant effect [21]. Assuming that, at baseline, they will report a mean of 4.26 days as in our pre-study (internal data), this reduction corresponds to a mean change by 2.13 days.The drop-out rate is conservatively estimated to be 20% in every group. Although for the analysis of the primary endpoint, missing values will be imputed by multiple imputation, we assume a reduction of 0 days in patients with missing data for a conservative estimation of the sample size.In the intervention group, the average change is therefore estimated to be (0 days) × 20% + (2.13 days) × 80% = 1.704 days. In the control group, the average effect is therefore estimated to be (0 days) × 20% + (1.14 days) × 80% = 0.912 days.Based on values in the pre-study, the standard deviation of the change is set to 3.19 days.Significance level and power are set to α=0.05 (two-sided) and 1-β=0.8.To detect this effect using a two-group *t*-test requires that 256 patients per group are randomized (nQuery 4.0) [32].

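### The primary analysis set drops randomized patients on headache counts that may come from follow-up, so the outcome can decide who is analysed

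*Protocol article*

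**What the plan says.** The Statistical analysis section of the protocol article states that "the primary hypothesis will be tested using a linear model in the FA analysis set". The FA set leaves out patients "in whom it becomes apparent after randomization that they have either (1) headaches other than migraine or tension-type", where tension-type headache accounts for more than half of the headache days per month, "or (2) 14 or more days with migraine headaches per month, are excluded".

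Under Endpoints, "days with migraine headache are counted from the electronic headache diary of the past 4 weeks at baseline and at follow-up 12"; the change between the two counts is the primary endpoint. ITT has a supporting role: "As a sensitivity analysis, all efficacy endpoints will be additionally evaluated in the intention to treat (ITT) and per protocol (PP) populations". On blinding, the Randomization section says: "The primary and secondary endpoints are based on patients’ assessment and therefore are not blinded".

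The entry rules bear on the same conditions. The Exclusion criteria rule out chronic migraine, other headache types, and tension-type headache unless it made up less than 50% of headache days per 4 weeks over the past 3 months. The 4-week baseline phase is used to confirm these criteria, and a further condition for randomization is "At least 3 reported migraine days according to inclusion criteria during the baseline phase (4 weeks" weeks). No entry limit of 14 migraine days is stated.

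**The concern.** A patient's migraine-day count after randomization is the primary outcome, and treatment can change it. If the same count can remove the patient from the primary set, the arms compared are no longer the arms that were randomized. The tension-type rule has a similar weakness, because migraine days are part of its denominator and a patient can cross 50% by improving.

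The stake is the confirmatory claim. The FA test of the primary endpoint opens the testing sequence for all six secondary endpoints, and the results are meant for the regulator's assessment of the product. In an open-label trial, a removal rule with no stated data window and no blinded decision also leaves room for judgement that differs by arm.

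**Working it through.** **1. How the rules act on the outcome.** Let b be the baseline count and f the count at follow-up 12, so the endpoint is y = f - b. If the 14-day rule is applied to f, no patient with y >= 14 - b can appear in the primary analysis.
- At the plan's mean baseline of 4.26 the cut is a rise of 14 - 4.26 = 9.74 days, or 9.74/3.19 = 3.1 of the plan's SDs of change. It is rarely reached.
- At a baseline of 10 the cut is a rise of 4 days, or 4/3.19 = 1.25 SDs. Randomization is stratified at 8 days, so patients well above the mean are expected.
- Tension-type rule: 5 migraine and 4 tension-type days give 4/9 = 44% (kept). If migraine days fall to 2, the share is 4/6 = 67% (removed).

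**2. Consistency with the missing-data plan.** Under Missing data, an intervention (IV) patient who stops the diary for lack of effect stays in and is imputed from the control (CO) distribution. An IV patient who keeps the diary and reaches 14 days can be deleted.

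**3. Size under uniform benefit.** The documents give no count distribution, so these are illustrations with gamma-Poisson day counts and at least 3 days at baseline.

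Both rules, rates cut by 30% in IV and 12% in CO:
- Baseline 4.5-5.2 days: the 14-day rule removes at most 0.1% of IV and 0.4% of CO. The estimate shifts toward zero by about 1-5% (for example -0.79 to -0.76). The SD of change is 2.3-2.7, below the plan's 3.19.
- Matching an SD of 3.19 in these runs takes a baseline near 6.5 days and gives roughly 11-14%.
- Baseline 6-7 days: about 10-23%.

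14-day rule alone, with a larger assumed spread:

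| Baseline mean | SD of change | All randomized to FA, rule at follow-up 12 | All randomized to FA, rule at any follow-up window |
|---|---|---|---|
| 4.8 | 3.0 | -0.719 to -0.663 (8%) | -0.724 to -0.649 (10%) |
| 5.5 | 3.5 | -0.929 to -0.798 (14%) | -0.930 to -0.769 (17%) |
| 6.0 | 4.1 | -1.107 to -0.831 (25%) | -1.094 to -0.760 (31%) |

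Each percentage is 1 - FA/all randomized. Removal ranges from 0.2% of IV and 0.7% of CO in the mildest case to 4.2% and 10.0% in the widest. The spread therefore matters as much as the mean.

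The tension-type rule mostly costs patients and shifts the estimate little. With 0.5 non-migraine days per 4 weeks it removes about 3-8% of IV; with 1-2 days, about 8-20% of IV and 6-16% of CO. These inputs are assumed.

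**4. False-positive rate** (14-day rule, 256 per arm, same settings as the table).
- Identical outcome distributions in both arms: FA rejects in 4.0-5.7% of trials, so there is no inflation.
- Mean effect about zero, with 25% of IV patients worsening: FA removes more IV than CO patients (1.7% versus 0.6% up to 12.8% versus 9.9%), shows a benefit of 0.16-0.52 days and rejects in 11-46% of trials. The all-randomized analysis rejects in 4.5-6%.

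**5. Power.** The plan's figure comes first: difference 1.704 - 0.912 = 0.792, SD 3.19, and "Significance level and power are set to α=0.05 (two-sided) and 1-β=0.8". The noncentrality is 0.792/(3.19 × √(2/256)) = 2.809. The exact t calculation gives power 0.8006, so 256 per group reproduces. Dropout is already in the diluted difference; FA exclusions are not. From loss of numbers alone:
- 1% excluded (253 per arm): 79.6%
- 2% (251): 79.3%
- 5% (243): 78.0%
- 10% (230): 75.7%

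The percentages excluded are assumed. The test is the unadjusted t-test of the sample-size section; the planned baseline-adjusted model is normally more precise.

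**The case against.** The best defence is that the FA set only removes patients found late to have been ineligible. The text speaks of a condition that patients have and that becomes apparent, and both rules resemble entry exclusions. An article may also leave the operational window to an analysis plan that is not shown.

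Part of this stands: the text does not state outright that follow-up counts trigger removal. But it does not exclude them, and two features count against the defence. No entry criterion sets a limit of 14 migraine days, so that rule does not restate a listed one. The tension-type rule in the FA definition also lacks the 3-month look-back that the entry version has. Since the baseline diary is checked before randomization, a count that emerges afterwards is most naturally read as a follow-up count. The article fixes the rule and attaches it to the confirmatory test, so this is not mere silence.

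The planned ITT analysis would expose a discrepancy. That mitigates the problem but does not change which set carries the test.

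Three stronger readings are tempting and not supported:
- A reader might infer that entry has no upper bound. The exclusions of chronic migraine and predominant tension-type headache, checked in the baseline phase, contradict that; only an explicit 14-day count is absent.
- A reader might infer that the rule favours the product. Under uniform benefit it dilutes the effect, and with identical arms it does not inflate the type I error.
- A reader might take a large shift as established. The larger figures need a baseline or spread above what the plan reports.

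**Conclusion.** The point holds. The primary analysis set is defined so that a post-randomization, treatment-affected count, which is the outcome itself, can remove patients, with no stated data window and no blinding of the decision. That is a design fault whatever its size.

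The size cannot be settled from the documents. Under the assumed 30% versus 12% reduction, the attenuation is about 1-5% near the plan's mean baseline and about 10-23% at 6-7 days, and larger if counts vary more than assumed there. The direction is not fixed: a false benefit is possible, but it was shown only under an assumed worsening in a quarter of IV patients. Power would fall to about 78% or 76% if 5% or 10% were excluded, and hardly at all at 1-2%.

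**What to change.** Name the set of all randomized patients (ITT), with the jump-to-reference imputation already planned, as the primary analysis set, and keep the present FA set as a sensitivity analysis.

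If the sponsor wishes to keep FA as primary, the minimum is to limit its exclusions to facts established from data recorded before randomization (inclusion visit and baseline diary), judged by someone blind to arm.

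Either way, reconcile the two FA limits with the Exclusion criteria and the Baseline assessment section, which state no 14-day limit and measure the tension-type share over a different window.

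The cost is wording in the protocol and analysis plan. The ITT analysis is already planned and the sample size stays at 256 per group. The downside is that a few ineligible patients remain in the primary analysis.
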